Key secondary outcome(s)	The following secondary outcomes related to clinical effectiveness will be measured at the participant level during follow-ups at 3, 6, and 12 months, unless otherwise specified below: 1. Body mass index (BMI) calculated using the formula: BMI = weight (kg)/height (m^2^), where height is measured in metres and weight is measured in kilograms 2. Blood pressure measured using an automated blood pressure instrument 3. Waist circumference measured in centimetres 4. Depression severity measured using PHQ-9 at 3 and 12 months 5. Depression caseness measured using PHQ-9 6. Anxiety caseness and severity measured using Generalised Anxiety Disorder Questionnaire (GAD-7) 7. Quality of life measured using Euroqol’s instrument EQ-5D-5L 8. Functional impairment measured using the WHO Disability Assessment Schedule (WHODAS 2.0) at 6 and 12 months 9. Healthcare resource measured using modified Client Service Receipt Inventory (CSRI) at 6 and 12 months 10. Adverse events measured using a modified adverse event The following clinic-level aggregated secondary outcomes related to implementation effectiveness will be calculated at 3, 6, and 12 months follow-up timepoints, unless otherwise specified below: 11. Reach of screening (RS) calculated using the formula RS = sd/nc, where ‘sd’ represents the number of individuals screened for depression and ‘nc’ denotes the total number of individuals attending the clinics 12. Reach of depression treatment (RT) calculated using RT = st/ne, where ‘st’ represents the number of individuals who participated in the treatment for depression and ‘ne’ represents the number of people eligible for such treatment at 3 and 12 months 13. Adoption (AD) calculated using AD = r/nr, where ‘r’ denotes the number of people referred for the treatment of depression and ‘nr’ denotes the number of people eligible for referrals at 3, and 6 months 14. Treatment enrolment (TE) calculated using TE = te/ne, where ‘te’ represents the number of people enrolled in the treatment of depression and ‘ne’ represents the number of people eligible for such treatment 15. Treatment completion (TC) calculated using TC = tc/te, where ‘tc’ represents the number of people completed the depression treatment and ‘te’ the number of people enrolled in such treatment 16. Treatment drop (TD) calculated using TD = td/te, where ‘td’ represents the number of people dropped out of the depression treatment and ‘te’ the number of people enrolled in such treatment 17. Sustainability calculated using change in percentage from baseline to follow-up time-points in reach, adoption, treatment enrolment, completion, and dropout 18. Equity by comparing reach, adoption, treatment enrolment, completion, and dropout across different levels of socioeconomic status, gender, and ethnicity

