#### Secondary outcomes—implementation

Secondary implementation outcomes include:The reach of screening as the percentage of people attending clinics who participated in screening for depression (PHQ-2 and PHQ-9) at least once.Adoption of the intervention will be determined at 3 and 6 months through referral rates (number of patients referred for treatment divided by number of eligible patients). We will consider referrals, including within primary care settings and to specialised facilities if required. We will track the number of healthcare staff invited to training, those who attend, and the average number of supervision or case review meetings attended by staff each month. These metrics will be assessed in the 3rd and 6th month follow-up after the start date.The implementation of the CC components will be assessed using treatment engagement and dropout rates. We will determine the enrollment, completion, and dropout rates for psychotherapy (BA therapy in intervention clinics and any psychotherapy delivered in control clinics). Individuals who attend ≥ 2 sessions will be categorised as ‘engaged with BA/any psychotherapy’, whereas those attending < 2 sessions will be considered dropouts. We will also evaluate the prescription and adherence rates of antidepressants using the total number of antidepressants prescribed and the participants who complete their prescribed course of antidepressant medication captured through patient self-reporting.Sustainability will be assessed by comparing reach, BA completion and dropout, antidepressant prescription, and compliance rate over time.Equity in the treatment is the just distribution of treatment services, ensuring the participation of all individuals regardless of their socioeconomic status (SES) and demographic backgrounds. To ascertain equity, we will compare implementation outcomes mentioned above by SES and demographics (age, sex, ethnicity, education level).

Unless otherwise stated above, all outcomes will be recorded and compared across allocation groups, where feasible at all time points (3, 6, and 12 months after the start date).

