### Statistical methods

Statistical analysis will be conducted using STATA version 18 (StataCorp, College Station, TX). All statistical tests will use 5% significance levels and 95% confidence intervals. Descriptive statistics (mean, standard deviation, counts, and percentage) shall be used to summarise both effectiveness and implementation outcomes at baseline and 3-, 6-, and 12-month follow-up time points by allocation groups. Assumptions of all parametric tests (such as normal distribution) where applicable and the presence of missing data at random will be evaluated; if not met, appropriate transformation or multiple imputation methods will be considered.

A mixed effects linear regression model will be used with a PHQ-9 score at 6 months as the outcome for the primary effectiveness endpoint. We will use the PHQ-9 baseline score and other important baseline variables as fixed effects and clinics as random effects to account for the clustered nature of the data. The same models (or logistic mixed effects model in case of binary outcome) will be used for other individual-level secondary variables, where applicable. All the analyses will be based on the intention-to-treat principle.

On the other hand, generalised linear model with a log link function and binomial distribution will be used for ‘reach’ (participants who received treatment divided by those eligible for treatment) as an aggregated implementation outcome to compare allocation groups while using some important clinic-level factors as covariates such as availability of EMR (present vs absent) and average attendance per month (small < 1000, medium 1001–3000, large > 3000). All other clinic-level data will be analysed using the same model, where comparisons across groups are applicable. Some clinic-level data captured only in the intervention group, such as adoption, will be summarised using descriptive statistics.

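### Treatment completion and dropout are compared between arms among enrolled people only, so collaborative care can look worse while more of its eligible patients complete or stay in treatment

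*Protocol article*

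**What the plan says.** Among the key secondary outcomes in Table 1 of the protocol article, items 14 to 16 form a chain. Enrolment is taken over eligible people: "Treatment enrolment (TE) calculated using TE = te/ne, where ‘te’ represents the number of people enrolled in the treatment of depression", divided by ne. Completion and dropout are then taken over those who enrolled: "Treatment completion (TC) calculated using TC = tc/te", with tc the number completing, and "Treatment drop (TD) calculated using TD = td/te, where ‘td’ represents the number of people dropped out of the depression treatment". In both, te is the number enrolled.

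The section *Secondary outcomes—implementation* says that these rates cover "BA therapy in intervention clinics and any psychotherapy delivered in control clinics". It sets one dropout rule for both arms, fewer than two sessions. It adds that, unless stated otherwise, "all outcomes will be recorded and compared across allocation groups", where feasible at each time point. *Statistical methods* follows the log-binomial model for reach with: "All other clinic-level data will be analysed using the same model, where comparisons across groups are applicable". Its example of data captured only in the intervention group is adoption, not completion or dropout.

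The primary implementation outcome, reach of treatment, uses all people with PHQ-9 of 10 or more as its denominator and counts those with at least two contacts.

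**The concern.** Randomisation makes the clinics comparable, and with them the eligible patients they find, provided both arms find them in the same way. It does not make the people who enrol in treatment comparable. Enrolment follows allocation, and the collaborative care model and its implementation strategies are meant to increase it. If collaborative care draws in people who would not otherwise have started treatment, and those people are less likely to stay, its per-enrolled completion falls and its per-enrolled dropout rises, even if nobody does worse than they would have under control. This needs no difference in screening or in the number eligible.

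At stake is the reading of the Implementation domain. A reported contrast could say that collaborative care has poorer completion or more dropout when a larger share of eligible patients completed or stayed.

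**Working it through.** **Inputs.** The formulas TE = te/ne, TC = tc/te and TD = td/te come from Table 1. The common dropout threshold (fewer than two sessions) comes from *Secondary outcomes—implementation*. The article gives no expected enrolment, completion or dropout rate, so there is no planned figure to reproduce. The 720 in *Sample size* concerns the PHQ-9 outcome and does not bear on this point. All rates below are assumptions. CC is collaborative care and OUC is optimised usual care.

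**Identity.** tc/ne = (te/ne) × (tc/te) = TE × TC. CC therefore scores worse on TC but better on completers per eligible person when

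TE_CC / TE_OUC > TC_OUC / TC_CC > 1.

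**Completion, how the reversal arises.** Suppose 40% of eligible people would enrol in either arm and 65% of them complete. CC also enrols a further 20% of eligible people, of whom 35% complete.

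- TC in CC: (0.40 × 0.65 + 0.20 × 0.35) / 0.60 = 0.33 / 0.60 = 55%. TC in OUC: 65%. Ratio 0.55 / 0.65 = 0.85.
- tc/ne in CC: 0.33. In OUC: 0.40 × 0.65 = 0.26. Ratio 0.33 / 0.26 = 1.27.
- Condition: 0.60 / 0.40 = 1.50 exceeds 0.65 / 0.55 = 1.18.

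**Completion, range of assumptions (CC v OUC).**

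| TE | TC | TC ratio | tc/ne | tc/ne ratio | TE ratio: needed / actual | Reversal |
|---|---|---|---|---|---|---|
| 70% v 30% | 50% v 70% | 0.71 | 35% v 21% | 1.67 | 1.40 / 2.33 | yes |
| 60% v 40% | 50% v 60% | 0.83 | 30% v 24% | 1.25 | 1.20 / 1.50 | yes |
| 50% v 45% | 50% v 60% | 0.83 | 25% v 27% | 0.93 | 1.20 / 1.11 | no |
| 40% v 40% | 50% v 60% | 0.83 | 20% v 24% | 0.83 | 1.20 / 1.00 | no |

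**Dropout, under the plan's common rule.** If dropouts are those with fewer than two sessions, the share of eligible people attending at least two is TE × (1 − TD) = (te − td)/ne. With TE 70% v 30% and TD 30% v 20%:

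- TD is higher in CC: 30% v 20%.
- At least two sessions among eligible: 0.70 × 0.70 = 49% v 0.30 × 0.80 = 24%, in favour of CC.

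**Why td/ne is no remedy.** With the same inputs, td/ne is 0.70 × 0.30 = 21% v 0.30 × 0.20 = 6%, ratio 3.5 against CC, compared with 1.5 on td/te. In the first illustration, if every non-completer counted as a stopper, td/te is 45% v 35% (ratio 1.29) and td/ne is 0.60 × 0.45 = 27% v 0.40 × 0.35 = 14% (ratio 1.93). The measure rises with enrolment itself, and an arm that enrolled nobody would score zero.

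**The case against.** The strongest reply is that the eligible denominator is already in the plan. Reach counts people with at least two contacts among all eligible, and TE is reported beside TC, so a reader can multiply the two and see the whole cascade. This is largely fair, and it limits the harm. It does not remove the point. Reach stops at two contacts and says nothing of completion. No comparison of tc/ne is planned, and its confidence interval does not follow from TE and TC modelled separately. The named TC and TD contrasts would still be reported as effects of allocation.

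Secondly, the comparison is qualified (where feasible, where applicable), and Table 3 labels the rows as BA completion and BA dropout. The qualifiers stand, but control-arm psychotherapy is expressly named for these rates, so a comparison is the natural reading.

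Thirdly, the enrolment gap may be small. Both arms have the same two-step screening, a counsellor on site, and therapy for those scoring 10 or more. That is possible, and the last two rows of the table show no reversal in that case.

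A reader might also infer two stronger points that the article does not support:

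- **That each arm is judged against its own course of therapy.** For dropout this is wrong, because one threshold serves both arms. For completion, the article defines no completed course and gives no session numbers. That definition may sit in the full protocol or analysis plan, so a differing yardstick cannot be asserted.
- **That the problem carries into arm contrasts for sustainability and equity.** Table 1 defines these as change from baseline and as comparison across socioeconomic status, gender and ethnicity, not as contrasts between arms.

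**Conclusion.** The point holds in limited form. TC and TD condition on enrolment, an event after randomisation that the intervention aims to change, and the article plans to compare them between arms where feasible. The direction of the completion contrast can oppose that of completers per eligible person: 0.85 against 1.27 in the illustration, and 0.71 against 1.67 in the most extreme case tried. Dropout can mislead in the same way. Whether this happens depends on rates the article does not give, and it does not happen when enrolment is equal or nearly so. It would be wrong to conclude that the trial's main findings are at risk: both outcomes are secondary, and neither PHQ-9 at 6 months nor reach is affected. This is an inexpensive improvement, worth making.

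**What to change.** - Make the between-arm completion comparison tc/ne, completers among all people with PHQ-9 of 10 or more, in the same clinic-level model as reach.
- Report tc/te and td/te by arm as descriptive figures beside te/ne, without a between-arm test.
- For retention, compare the share of all eligible people attending at least two sessions, the threshold the article already applies to both arms. Do not compare td/ne.

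The counts tc, td, te and ne are already in the plan's formulas, so the cost is wording in the analysis plan and the registry entry. The downside is that the per-enrolled rates become descriptive. The eligible denominator still relies on both arms finding eligible people in the same way, which the shared screening procedure is meant to secure. Recruitment was still open at the last status report (598 of 720 by 15 January 2026). The change should be dated and recorded before clinic-level data are examined by arm.

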
### Study setting

The study will be based in primary care clinics of SINA Health, Education and Welfare Trust [35], which is a not-for-profit trust that has established 38 primary care clinics in the most impoverished areas of Karachi, Pakistan. SINA offers comprehensive primary healthcare services, including a limited mental health programme, providing treatment to around 1.5 million people annually. SINA clinics serve the most economically deprived populations, providing healthcare at a minimal cost or free of charge, for those assessed to be entitled for welfare. They are relatively well-resourced, including the use of electronic medical records (EMR) in the majority of the clinics. SINA clinics are categorised into three main types of facilities based on the number and type of staff available, and the services they offer: (i) availability of > 2 primary care physicians (PCP) and a lay counsellor (*N* = 10), (ii) those with > 2 PCP but no lay counsellor (*n* = 17), and (iii) those staffed with only one PCP (*n* = 11). Lay counsellors are non-specialist mental health care providers without any formal education in mental health. They receive training to screen for common mental disorders, including depression, using simple tools such as Patient Health Questionnaire-9 (PHQ-9), and are trained to deliver brief psychological therapy suited for non-specialists. They also refer patients to mental health specialists when more intensive care is needed. Their work is carried out under the supervision of qualified mental health professionals [36]. Presently, only a few clinics offer antidepressant medications.

### Eligibility criteria

All patients ≥ 18 years attending the trial primary care facilities with depression symptoms identified following screening with PHQ-9 having a score of ≥ 10, will be eligible to take part in the study. Those already receiving any psychological therapy, lacking the capacity to provide informed consent, or not willing to participate will be excluded.

The PHQ-9 includes nine items and is scored on a scale from 0 to 3 according to the frequency of experiencing the symptom during the last 2 weeks, ranging from ‘not at all’ to ‘nearly every day.’ The total score ranges from 0 to 27. Scores between 0 and 4 indicate absence of depressive symptoms; 5–9 mild depressive symptoms; 10–14 moderate depressive symptoms; 15–19 moderately severe depressive symptoms; and 20–27 severe depressive symptoms [37, 38].

### Randomisation

Randomisation will be at the primary care clinic level which will be the ‘cluster’. Minimisation technique will be used to achieve balance on three characteristics: (i) clinic size or average attendance per month (small < 1000, medium 1001–3000, large > 3000), (ii) availability of EMR (present/absent) and (iii) counsellors (previously present/absent). Once all clinics are recruited, randomisation of the clusters will be undertaken by the York Trials Unit using minimPy [39] (See Fig. 1).

**Fig. 1 Fig1:**
[figure not shown]
CONSORT flow diagram

### Recruitment

Recruitment of patients will be based on a two-stage screening process. All patients attending the trial clinics will be screened by trained PCPs for depressive symptoms initially using the PHQ-2 (a brief version of PHQ-9). Patients screening positive on PHQ-2 (score ≥ 3) will be referred to the counsellors for assessment using the PHQ-9. This will be implemented as part of routine practice in both the intervention and control clinics. To balance the intervention and control clinics except for the intervention, we plan to recruit counsellors for those trial clinics which do not have counsellors present currently.

In the intervention clinics as part of the CC model, patients who screen positive on PHQ-9 (score 10 or above) will be offered BA therapy, antidepressants, or their combination as per treatment protocol. In control clinics, optimised usual care (OUC) will be offered, including information leaflets and routine psychological treatment. Patients who fulfil the trial inclusion criteria will be approached by the researcher present, who will provide the study information sheet in the local language. Written informed consent will be obtained before trial enrolment. Where there are issues of literacy, the information will be read out by researchers and understanding checked; consent will be recorded via thumbprint signatures. Potential participants will be informed that their decision to take part in the study will not affect their entitlement to usual services and that they are free to withdraw from the study at any stage without having to provide a reason. If participants are willing to provide reasons for withdrawal, this will be recorded in the change of status form. There are no cross-overs intended as part of the trial design, and cross-overs of the trial participants between the intervention and control clinics are less likely to happen because of the separate catchment areas that the different clinics serve. However, the central electronic records system will help identify any potential cross-overs, in the unlikely case of it happening.

### Baseline assessments

All consenting participants will undergo baseline assessment at recruitment or within 1 week through a questionnaire and clinical assessments to record demographics (age, sex, ethnicity) [40], education, language(s), employment status, socioeconomic status [41], household expenditures, productivity loss, history of depression, chronic physical health conditions (diabetes, cardiovascular disease, lung disease), other mental illness, current depression [37] and anxiety severity [42], quality of life [43], functional impairment [44], healthcare resource use [45], body mass index (BMI), blood pressure (BP) and blood tests (haemoglobin, glycosylated haemoglobin (HBA1c)) (see details of tools in outcomes section).

### Blinding

Blinding to the intervention will not be possible for study participants, or those involved in its delivery, due to its nature. We will endeavour to keep researchers involved in recruitment, baseline and outcome data collection to remain blinded to the allocation of clinics. However, there is a risk that this cannot be maintained if there are visible changes to clinics because of implementation strategies. We will check the maintenance of blinding during and at the end of the trial.

### Interventions

Our main intervention inputs are (i) the CC model and (ii) implementation strategies to support contextually adapted CC model for depression in the intervention clinics.

The implementation team (IT) led by two implementation champions from SINA, including clinic staff (PCPs, lay counsellors, clinic supervisors), SINA management (programme manager, mental health programme officer, quality assurance manager, and assistant manager of data analytics), and research team members, helped devise implementation strategies and finalise components of the CC model during the co-design stage previously, through involvement of the service users, carers, and community members. The implementation strategies were then refined through rapid testing and feedback from staff and service users across six test clinics (details will be reported in a separate publication).

#### Collaborative care model

The CC components co-designed considering the SINA context include the following: (i) two-stepped systematic identification of depression for all people aged ≥ 18. In the first stage, PCPs will screen patients using the PHQ-2, those scoring ≥ 3 will be referred to the lay counsellor. In the second stage, the counsellors will use the PHQ-9 to identify depression; (ii) counsellors will offer BA [38] therapy to patients scoring ≥ 10 on the PHQ-9. If a patient does not respond or prefers antidepressants, counsellors will refer the patient to the PCP to initiate antidepressant treatment; (iii) counsellors will track and monitor depression (e.g. the severity of depression symptoms) and process measures (e.g. number of contacts, care provided, and review with the mental health specialist) for all patients currently receiving care; (iv) counsellors and PCPs will collaboratively adjust care, using a stepped care approach such as augmenting BA with medication or changing the medication dose until care goals (improvement or remission of depression) are achieved; and (v) counsellors and PCPs (if required) will attend weekly supervision and case review meetings with the mental health specialists (See Fig. 2).

**Fig. 2 Fig2:**
[figure not shown]
Collaborative care model implementation

#### Implementation strategies

The co-designed implementation strategies based on Expert Recommendations for Implementing Change (ERIC) [46, 47], to support the implementation of contextually adapted CC are provided in Table 2.

**Table 2 Tab2:** List of implementation strategies to be used as part of the SPIRIT-D trial

Implementation strategies*	Description
